## Measurement

### Basic information

Basic information collected included age, gender, educational level, marital status, living alone status, monthly income, body mass index (BMI), weekly exercise frequency, and number of falls.

### Primary outcomes

Primary outcome assessments focused on multidimensional balance ability (static, dynamic, proactive, reactive, and daily living balance), hand function (grip strength and manual dexterity), and life-space mobility.

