**Methods:**

A single-blind, four-group parallel, multicenter randomized controlled trial was used. Four rural communities in Huzhou, Zhejiang Province, were included in the study, with an estimated total sample size of 132 individuals. During the 16-week intervention period, the comprehensive exercise program consisted of two balance training programs and one hand training session provided by a multidisciplinary team including physiotherapists, sports professionals, nurses and community health workers. The four rural communities were randomly divided into four experimental groups in the ratio of 1:1:1:1 (a) static balance training combined with hand training; (b) dynamic balance training combined with a hand training program; (c) multi-modal static-dynamic balance and hand function training (M-mBHF) program; and (d) a Daily activity group. The multidimensional balance ability, hand function, and life-space mobility of the four parallel groups will be assessed at baseline (T0), 8 weeks of intervention (T1), 16 weeks of intervention (T2), and at 24 (T3) and 32 weeks (T4) follow-up.

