### Sample size

Based on a previous study evaluating the impact of proprioceptive balance training on posture control in older adults [19], G*Power 3.1 was used for power analysis to determine the required sample size for detecting a statistically significant effect of the intervention [20]. The significance level (α) was set at 0.05, and the statistical power was set at 0.80. To account for an anticipated 10% dropout rate over the 16-week study period, 33 participants will be recruited per group.

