### Dynamic balance ability

Was assessed using the Biodex Stability System (BSS; Biodex Medical Systems, Shirley, NY, USA), which features a 360° rotating platform with a maximum tilt of 20° [24]. Specialized software (Biodex, Version 1.32) used indices such as the Overall Stability Index (OSI), Anterior-Posterior Stability Index (APSI), and Medial-Lateral Stability Index (MLSI) for evaluation. APSI and MLSI represent platform displacements in the sagittal (Y) and frontal (X) planes, respectively, while OSI is their composite score (OSI = [(Σ(0– Y)² + Σ(0– X)² / samples)]^0.5).[25] Lower scores indicated better balance. Testing occurred in a quiet setting. Participants stood barefoot, one-legged, with eyes open, knees bent 15°, arms down, and feet on markers. After a 1-minute adaptive training and three practice trials to minimize anxiety and learning effects, the official test involved an 8-level stability test (most stable level) [26]. Each 20-cycle had automatic tilting. Three trials were conducted with a 10-second rest between them, and the average score was computed.

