### Data analysis

SPSS 26.0 software was used for statistical analysis, with a significance level set at *p* < 0.05. Initially, the Shapiro-Wilk test will be employed to assess the normality assumption for quantitative data. Based on these results, appropriate statistical methods will be selected to compare participants’ demographic and other baseline characteristics before the intervention. If the data are normally distributed, an independent-sample t-test will be utilized; otherwise, the Mann-Whitney *U* test will be applied. The primary outcome measures, continuous variables, were analyzed using generalized estimating equations (GEEs). In cases of significant interactions between group and time factors, a simple effects analysis will be conducted to elucidate the sources of the differences. If the simple effects analysis of time factors yields significant results, post hoc tests will be performed using the Sequential Bonferroni Procedure to identify specific time points of substantial differences. Secondary outcomes included descriptive statistics on exercise adherence after intervention.

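### Eight unranked primary outcomes are each tested at 0.05 with no error control across them, and the stated power and the 16-week dropout allowance do not cover that claim or the follow-up to week 32

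*Protocol article*

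**What the plan says.** - **Outcomes.** The Primary outcomes section of the protocol article says that the primary assessments focus on "multidimensional balance ability (static, dynamic, proactive, reactive, and daily living balance), hand function (grip strength and manual dexterity), and life-space mobility". That is five balance domains, two hand-function domains and life-space mobility, eight in all. None is ranked above another. The subsections that follow give one instrument per domain. For dynamic balance, the Biodex system "used indices such as the Overall Stability Index (OSI), Anterior-Posterior Stability Index (APSI), and Medial-Lateral Stability Index (MLSI) for evaluation".
- **Times.** The abstract has the outcomes "assessed at baseline (T0), 8 weeks of intervention (T1), 16 weeks of intervention (T2), and at 24 (T3) and 32 weeks (T4) follow-up". No time is named as primary.
- **Analysis.** The Data analysis section sets one significance level, p < 0.05, and analyses the primary measures by GEE. A significant group-by-time interaction opens a simple effects analysis. If the time effects in that analysis are significant, "post hoc tests will be performed using the Sequential Bonferroni Procedure to identify specific time points of substantial differences". No other correction is stated.
- **Size.** The Sample size section says that power was computed "to determine the required sample size for detecting a statistically significant effect of the intervention", and that "The significance level (α) was set at 0.05, and the statistical power was set at 0.80". It names no outcome, time point, contrast, test or effect size. It continues: "To account for an anticipated 10% dropout rate over the 16-week study period, 33 participants will be recruited per group".

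**The concern.** The plan fixes which outcomes are primary, the level for testing them and the scope of its correction. That scope is time points within an outcome. Eight primary outcomes therefore each get their own opening test at 0.05, and nothing limits the chance that one of them succeeds by luck. A reader of the results could not tell a real effect on one primary outcome from the one or two chance findings that eight tests can produce.

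The sample size has the matching problem. One alpha and one power describe one test. They do not say how likely the trial is to support a claim that is protected over eight primaries. The dropout allowance is tied to 16 weeks, yet the same primary outcomes are assessed again at weeks 24 and 32.

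**Working it through.** **Inputs from the protocol article.** Eight primary outcomes (Primary outcomes); level 0.05 (Data analysis, Sample size); power 0.80, 33 per arm, 10% dropout over 16 weeks (Sample size); 132 in total and assessments to week 32 (Abstract).

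**Assumptions.** A common correlation between outcomes of 0.3 to 0.7. An effect size solved backwards from the sample size. After week 16, the same rate of loss as before.

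**1. The plan's own figure.** 4 × 33 = 132 agrees with the abstract. The step from effect size to 33 cannot be reproduced, because no effect size, SD or test is given. What can be seen is that 33 follows from 30 × 1.1 = 33, or from 29 / 0.9 = 32.2, rounded up to 33. The evaluable number is thus about 29 to 30 per arm, and 33 × 0.9 = 29.7.

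**2. False positives over eight outcomes.** Count one 0.05 test per outcome, the group-by-time interaction, because later comparisons open only after it.
- Independent outcomes: 1 − 0.95^8 = 1 − 0.663 = 0.337.
- Equally correlated outcomes, simulated with two-sided normal tests as a stand-in for the interaction test:

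| Common correlation | P(at least one false positive) |
|---|---|
| 0.3 | 0.30 |
| 0.5 | 0.25 |
| 0.7 | 0.19 |

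**3. Power at an error-controlled level.** Solve for the effect that 30 per arm detects with 80% power at 0.05, then change only alpha. The first Holm step over eight outcomes uses 0.05 / 8 = 0.00625.

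| Test | Back-solved effect | Power at 0.05 | Power at 0.00625 |
|---|---|---|---|
| Two-sample t, two-sided | d = 0.736 | 0.80 | 0.51 |
| Four-group one-way ANOVA | f = 0.307 | 0.80 | 0.52 |

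Starting from 29 per arm (d = 0.749, f = 0.312) gives the same powers to two decimals.

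**4. What would restore 80%.** By the normal formula for two means, n scales with (z for alpha + z for power)². So 30 × ((2.734 + 0.842) / (1.960 + 0.842))² = 48.9, or 49 evaluable per arm, and 49 / 0.9 = 54.4, or 55 recruited. The ANOVA version gives 47 evaluable and 47 / 0.9 = 52.2, or 53 recruited. The plan has 33.

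**5. Loss beyond week 16.** If a further 10% of those remaining were lost by week 32, 33 × 0.9 × 0.9 = 26.7 per arm would be left. At d = 0.736 and alpha 0.05 the two-sample t-test then has power of about 0.75. To keep 29 to 30 per arm at week 32, 29 / 0.81 = 35.8 to 30 / 0.81 = 37.04 would be needed, that is 36 to 38 recruited.

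**The case against.** **The time dimension is not unprotected.** A reader might multiply eight outcomes by four follow-up times, or by three comparisons with control, and infer that the plan runs dozens of free tests at 0.05. The text does not support this. The interaction test comes first, and time points then go through Sequential Bonferroni. Contrasts that share one control group are also not independent. With no true effects, the interaction test keeps the gated false positives for an outcome to about 5%, however many arm comparisons follow. That stands, and it is why the working counts one test per outcome. It does not help across outcomes, because the gate itself is opened eight times.

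**Ten endpoints rather than eight.** One could count each Biodex index separately. The article introduces the indices as examples and describes the overall index as a composite of the other two, so they are not three independent endpoints. Eight is the defensible count.

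**This belongs in a SAP.** A SAP may well add detail. But the article itself designates the primaries, fixes the level and states what its multiplicity procedure is for. The point concerns those stated rules.

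**The power figures rest on an invented effect.** The effect is back-solved and appears nowhere in the article, and the planned analysis is a repeated-measures GEE, not a t-test or ANOVA. This stands as a limit on precision. The fall from 80% to about half comes mainly from the change in alpha and hardly depends on the starting n.

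**No success rule is stated.** It is true that the article nowhere says one significant primary is enough to call the program effective. If all eight had to succeed, alpha would need no splitting, but joint power would be about 0.8^8 = 0.17 for independent outcomes. The article states no such rule either.

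**Conclusion.** The point holds. With eight unranked primaries and no control across them, the familywise error is about 34% if outcomes are independent, and 30% to 19% at common correlations of 0.3 to 0.7. The stated 80% power does not describe an error-controlled claim. Under the back-solved effect it is about 51% to 52% for an outcome tested at 0.05/8. Holm can do better than this for outcomes tested at later steps, so the figure is a floor. The dropout allowance stops at week 16; under continued loss, unadjusted power at week 32 is about 75%.

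Two further inferences should be avoided. A reader might suppose that the Biodex overall index is the measure behind the sample size. The Sample size section mentions only a previous study on posture control and names no instrument. A reader might also suppose that week 16 is the only time the dropout allowance covers; week 8 falls within it too.

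All figures treat participants as independent. The Randomization section assigns whole communities to arms, which is a separate matter that the fix below does not resolve.

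**What to change.** **Preferred.** In the Primary outcomes and Data analysis sections, name T2 (week 16, the end of the intervention) as the primary time and apply Holm across the eight primary outcomes at that time. Holm needs exactly one p-value per outcome, so state which week-16 comparison from the GEE supplies it, and prespecify one Biodex index for dynamic balance. In the Sample size section, restate power at the first-step alpha of 0.00625, and say that the dropout allowance does not extend to T3 and T4. This keeps hand function and life-space mobility, both in the trial's title, among the primaries.

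**Alternative.** The sponsor names one primary outcome of its choice, matched to the outcome used for the sample size, and makes the others secondary. Alpha then stays at 0.05.

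**Cost.** Changes of wording and a registry update before analysis. The first route gives a less favourable stated power unless more participants are recruited; the second narrows the headline claim.

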### Static balance ability

Was evaluated using the One Leg Stand Test (OLST). Participants were instructed to lift one leg off the ground (either leg), stand on the remaining leg with eyes open and gaze forward, and maintain this position for as long as possible. Timing began when one foot left the ground. Shorter durations indicated poorer balance function, with > 60 s considered good, 30–60 s fair, and < 30 s poor [23]. 

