### Randomization, allocation concealment, and blinding

Four rural communities in Huzhou, Zhejiang Province, were randomly selected to ensure comparability regarding economic development, cultural practices, and infrastructure. A minimum separation distance of 5 km between communities was maintained to minimize contamination risk. The investigator prepared slips labeled “Intervention groups (a)(b)(c)” and “control group” and placed them in sealed envelopes. Representatives from the four communities randomly selected envelopes and were assigned to the four groups on a 1:1:1:1 ratio. Research assistants received intervention information via sealed envelopes, while outcome evaluators and data analysts remained blinded to the intervention details. Due to the nature of the intervention, blinding participants was not feasible.

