### Intervention group

The M-mBHT program was developed by a multidisciplinary team comprising nursing specialists, physiotherapists, psychologists, sociologists, and geriatricians. This team adhered to the ICFSR guidelines to design an integrated training program tailored specifically for older adults in rural communities [21]. The static-dynamic balance training component was derived from balance posture control movements [22], while the hand training component was designed by [name], a senior gymnastics coach in Shanghai, using principles of traditional Chinese medicine. The program follows a cyclic training mode, consisting of one week of instruction followed by one week of practice, facilitating steady skill acquisition and internalization by older adults. Training intensity progressively increases through altered sensory inputs and external distractions. The comprehensive program includes four parts: (1) a 5-10-minute warm-up session (including wrist, hip, shoulder, knee, and ankle range of motion exercises); (2) a 15-minute static balance training session (standing on both feet, tandem standing, and one-foot standing); (3) a 25-minute dynamic balance training session (normal gait, narrow gait, overlapping gait, and tandem gait); and (4) a 10-minute hand training session (finger exercises, acupuncture point stimulation, and finger relaxation phases). Detailed information is provided in Table 1. Based on the components of the comprehensive program, the three intervention groups are designated as follows: (a) Static Balance Training with Hand Training, (b) Dynamic Balance Training with Hand Training, and (c) multi-modal static-dynamic balance and hand function training (M-mBHF).

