### Data collection and management

The data collection team consists of two medical graduate students and one community worker, primarily operating at rural community service centers. Data collectors must undergo standardized training and be fluent in local dialects. Table 2 shows the five measurement time points: baseline before randomization (T0), mid-intervention (T1), post-intervention (T2), and follow-up (T3 and T4). After data collection, participants’ identities will be anonymized using initial-number combinations, and handwritten records will be digitized. Two researchers will independently enter data into Excel. Software tools will detect inconsistencies and generate reports. After verification and cross-checking, data will be stored in an electronic database accessible only to principal investigators, data consultants, and data entry staff.

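### The One Leg Stand Test may be done on either leg and nothing carries the baseline leg forward, so changes of leg can add avoidable noise to a primary outcome

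*Protocol article*

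**What the plan says.** All references are to the Protocol article.

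- **Static balance ability.** Participants are told to "lift one leg off the ground (either leg") and to hold the position as long as they can. "Timing began when one foot left the ground". One timed stance is described, with no averaging over legs.
- **Primary outcomes.** "Primary outcome assessments focused on multidimensional balance ability (static, dynamic, proactive, reactive, and daily living balance"), together with hand function and life-space mobility. The One Leg Stand Test is the only measure listed for the static dimension.
- **Data collection and management.** "Table 2 shows the five measurement time points: baseline before randomization (T0), mid-intervention (T1), post-intervention (T2), and follow-up (T3 and T4").
- **Data analysis.** The continuous primary outcomes go into generalized estimating equations (GEE), and the follow-on tests depend on the group-by-time interaction.
- **Intervention group.** The static component, given to groups (a) and (c), is "a 15-minute static balance training session (standing on both feet, tandem standing, and one-foot standing").
- **Randomization, allocation concealment, and blinding.** "Due to the nature of the intervention, blinding participants was not feasible". Outcome evaluators and data analysts are blinded.
- **Dynamic balance ability.** The Biodex test is also done on one leg: "Participants stood barefoot, one-legged, with eyes open, knees bent 15" degrees. No leg is named.

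No section says that the leg used at baseline is recorded or used again.

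**The concern.** A group-by-time comparison asks whether people in one arm change more than people in another. It is most precise when the same thing is measured on the same person each time. If the stance leg is free, part of a person's apparent change between T0 and a later visit may be the difference between the left and right leg. That lowers the correlation between visits and widens the standard error of the comparison. The article plans 33 participants per group with 10% dropout allowed for, so there is little precision to give away. If the leg is not recorded, the loss cannot be repaired at analysis.

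**Working it through.** **The plan's own figure.** 33 × 4 = 132 agrees with the stated total. For dropout, 29/0.9 = 32.2, which rounds up to 33, and 30 × 1.10 = 33, so 33 fits about 29 or 30 evaluable per group. No effect size, standard deviation or correlation is given, so the evaluable number cannot be re-derived. The point does not depend on it.

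**Assumed inputs (none is in the article).**
- r: correlation between two visits on the same leg, 0.7 to 0.8.
- L: correlation between the error-free scores of the left and right leg, 0.8 to 0.9.
- p: share of participants whose leg at follow-up differs from their leg at T0, 25% to 50%. Choosing at random at each visit gives 50%.
- Equal variance for both legs and at both visits, and changes of leg unrelated to the score.

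**Formulas.**
- Effective correlation: r_eff = r × [(1 − p) + p × L]
- Change-score variance ratio: (1 − r_eff)/(1 − r)
- Baseline-adjusted variance ratio: (1 − r_eff²)/(1 − r²)

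**Results.**

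| r | L | p | r_eff | Change score | Baseline-adjusted |
|---|---|---|---|---|---|
| 0.8 | 0.8 | 0.50 | 0.8 × 0.90 = 0.72 | 0.28/0.20 = 1.40 | 0.4816/0.36 = 1.34 |
| 0.8 | 0.9 | 0.50 | 0.8 × 0.95 = 0.76 | 0.24/0.20 = 1.20 | 0.4224/0.36 = 1.17 |
| 0.7 | 0.9 | 0.25 | 0.7 × 0.975 = 0.6825 | 0.3175/0.30 = 1.06 | 0.5342/0.51 = 1.05 |
| any | 1.0 | any | r | 1.00 | 1.00 |
| any | any | 0 | r | 1.00 | 1.00 |

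The first and third rows are the extremes of the assumed range. A GEE with T0 among the repeated outcomes and a full group-by-time term compares mean changes, so with complete data the change-score column is the closer guide. The last column applies if T0 is used as a covariate.

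**What this means for power.** Suppose a two-arm comparison has exactly 80% power with the leg fixed (two-sided 5%). The expected effect is then 1.96 + 0.84 = 2.80 standard errors.
- Ratio 1.34: 2.80/√1.34 = 2.42, and 2.42 − 1.96 = 0.46, so power is about 68%.
- Ratio 1.05: 2.80/√1.05 = 2.73, and 2.73 − 1.96 = 0.77, so power is about 78%.

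This treats participants as independent and serves only to translate variance into power.

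**Possible bias between arms.** With r = 0.8 and normal scores in SD units, moving from a random leg to the better leg gains √[(r − r × L)/π] on average.
- L = 0.9: √(0.08/π) = 0.16 SD
- L = 0.8: √(0.16/π) = 0.23 SD

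The bias is this gain times the difference between arms in the share who make that move. At 25 percentage points it is 0.04 to 0.06 SD, and at 50 points 0.08 to 0.11 SD. If the share is the same in all arms, it is zero.

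**The case against.** **The sentence is only a starting instruction.** It does not mention visits or say that the leg is chosen afresh each time, and a free first choice is compatible with keeping that leg. Five free choices are an inference from two sections read together. The article condenses a fuller protocol, and data collectors receive standardised training, so an unseen manual may fix the leg. This stands in part. But the article does address which leg is used, leaves it open, and says nowhere that the choice is kept. Someone following the published text could change legs without deviating from it.

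**The size may be nothing.** The calculation reads L as a correlation between error-free scores. If 0.8 were instead the observed left-right correlation at one visit, with same-leg retest 0.8 and independent errors, the true correlation would be 0.8/0.8 = 1 and changing legs would cost nothing. People with a stable preference would also change seldom. Both arguments are correct, so the upper figures are not an estimate.

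**A reader might infer a spurious training effect.** Groups (a) and (c) practise one-foot standing and participants are unblinded, so one might expect trained participants to find and use their better leg. The article does not support this. Every arm gets the same instruction, evaluators are blinded, controls take the same test at the same visits, and anyone may already use the preferred leg at T0. Group (b) does not train the static component at all.

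**A reader might count the Biodex test as a second instance.** That section is silent on the leg rather than permissive, and an article may leave such detail to the full protocol. It is not a separate error.

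**Conclusion.** The point holds as one of precision. The published instruction leaves the stance leg open for the only measure of static balance, and nothing carries the baseline leg forward, so left-right differences can enter within-person change. Under the assumed values, baseline-adjusted variance rises by about 5% to 34% and change-score variance by about 6% to 40%. Both fall to zero if the legs are interchangeable or nobody changes leg. None of the correlations or switching shares comes from the article, so the true loss may lie anywhere from none to substantial. Bias between arms remains a possibility, not a finding. The test is one of eight measured primary domains (five of balance, two of hand function, and life-space mobility), and the article does not say that the sample size rests on it. Minor to moderate.

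**What to change.** In the section Static balance ability, replace the free choice of leg with a rule such as: *the participant chooses the stance leg at T0; it is recorded, and the same leg is used at T1 to T4*. The Biodex test can follow the same convention for consistency.

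The cost is one field on the assessment form, with no extra visits, staff or participants. If some T0 assessments were done without recording the leg, record it and hold it constant from the next visit. That protects comparisons among later visits, although the comparison with T0 stays exposed for those participants. Testing both legs at every visit with a stated summary would also work, at the price of a second stance each time.
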